## 3. Statistical Methods

### 3.1. Sample Size

Our study will include one group arm. According to our power analysis (F-test, Anova Repeated Measures, within factors), for a cohort of patients with three consecutive laboratory measurements, considering an effect size = 0.25, a = 0.05, and 95% power, 58 patients should be included in the study. To compensate for possible dropouts, the sample size was increased to 65 patients.

### 3.2. Statistical Analysis

The normality of our data will be tested with both the Shapiro–Wilk and the Kolmogorov–Smirnov tests. Fisher’s exact and chi-square tests will be used for the evaluation of differences between categorical variables, and the data will be presented as frequencies and percentages. Continuous variables, following a normal distribution, will be tested with the student’s *t*-test and will be presented as mean and standard deviation (SD), while the Mann–Whitney U test will be used for those without a normal distribution, and data will be presented as median and interquartile range (IQR). Anova Repeated Measures, parametric or nonparametric test, as appropriate, will be used for the evaluation of possible differences among parameters measured at different time points.

A univariate and multivariate analysis will be conducted using linear or logistic regression, as appropriate, with backward stepwise elimination for the assessment of independent risk factors contributing to our primary outcome. Our final multivariable model will include variables with *p*-values < 0.1 in the univariate regression, while the choice of variables will also be based on scientific knowledge. Variance inflation factor (VIF) will be used for the assessment of multicollinearity issues. Independent factors contributing to our primary outcome will be presented as odds ratio (O.R.) or regression coefficient and 95% confidence interval (CI) as appropriate.

Sensitivity and specificity analyses will also be performed using the Receiver Operating Characteristic Curves (ROC). Data will be analyzed using the Statistical Package for the Social Sciences (SPSS, version 28.0; IBM, Armonk, NY, USA) and GraphPad Prism Software (La Jolla, CA, USA, version 10.4.4), and *p*-values < 0.05 will be considered significant.

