### 1.3. Objectives

(1)To evaluate the early (postoperative day one) and late (postoperative day 3 or 4) effects of complex EVAR of para-renal and thoraco-abdominal aortic aneurysms on coagulation, with respect to von Willebrand factor (vWF), factors VIII and XI, D-dimers, fibrinogen, Adamts-13 levels, and platelet activation, in patients undergoing complex para-renal and thoraco-abdominal aortic aneurysm repair (primary endpoint);(2)To record the incidence of myocardial injury after non-cardiac surgery (MINS), major adverse cardiovascular events after non-cardiac surgery (MACE), acute kidney injury (AKI), post-implantation syndrome (PIS), and death from any cause during hospitalization;(3)To record the incidence of MACE, implant failure, or death from any cause at 30 days and 3, 6, and 12 months postoperatively.

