### 2.3. Study Schedule

Preoperatively and before induction to general anesthesia, the preoperative data, including demographics (age, gender, body mass index), American Society of Anesthesiologists physical status (ASA PS), any comorbidities and administrated drug therapy, smoking status and alcohol intake, the size of aneurysm, the type of graft used, and baseline liver and renal function will be recorded. In addition, a complete blood count, conventional coagulation tests, kidney and liver function tests, vWF, factors VIII and XI, D-dimers, fibrinogen, Adamts-13, platelet activation (multiplate), and high-sensitivity troponin will be obtained. The anti-Xa value will also be determined in order to rule out an anticoagulant effect on the laboratory tests.

At the first postoperative day, the duration of surgery and the possible occurrence of MINS, MACE, AKI, and PIS will be recorded, while a complete blood count, conventional coagulation tests, kidney and liver function tests, vWF, factors VIII and XI, D-dimers, fibrinogen, Adamts-13, platelet activation (multiplate), and high-sensitivity troponin will be obtained. The anti-Xa value will also be determined in order to rule out an anticoagulant effect on the laboratory tests.

At the 3rd or 4th postoperative day, based on the date of discharge, the length of hospitalization, the number of transfusion units, and the possible occurrence of MINS, MACE, AKI, and PIS will be recorded. In addition, a complete blood count, conventional coagulation tests, kidney and liver function tests, vWF, factors VIII and XI, D-dimers, fibrinogen, Adamts-13, platelet activation (multiplate), and high-sensitivity troponin will be obtained from a peripheral vein. The anti-Xa value, correlated to the weight and the dose of the anticoagulant, is also determined in order to rule out an anticoagulant effect on the laboratory tests.

At 1, 3, 6, and 12 months postoperatively, MACE, implant failure (including secondary sac rupture, graft explantation, type 1 or 3 endoleak, or major mitigation of the stent grafts), and death from any cause will be recorded. The study plan and data collection are summarized in Figure 1.

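### The primary objective asks for an early and a late effect, but the plan names only an omnibus test whose form is left open; one prespecified mixed model per marker with two contrasts against baseline would answer it better.

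*Protocol article*

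**What the plan says.** Section 1.3 (Objectives) sets the primary endpoint as two questions: "To evaluate the early (postoperative day one) and late (postoperative day 3 or 4) effects of complex EVAR", for von Willebrand factor, factors VIII and XI, D-dimers, fibrinogen, Adamts-13 and platelet activation.

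Section 3.1 (Sample Size) rests on a within-factor repeated-measures ANOVA F-test for three measurements in one group: "considering an effect size = 0.25, a = 0.05, and 95% power, 58 patients should be included in the study". It then adds: "To compensate for possible dropouts, the sample size was increased to 65 patients".

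Section 3.2 (Statistical Analysis) begins with "The normality of our data will be tested with both the Shapiro–Wilk and the Kolmogorov–Smirnov tests" and later says, of values taken at the several time points, "Anova Repeated Measures, parametric or nonparametric test, as appropriate, will be used for the evaluation of possible differences". Confidence intervals are mentioned only for the risk-factor regression.

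Section 2.3 (Study Schedule) times the third sample as follows: "At the 3rd or 4th postoperative day, based on the date of discharge".

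**The concern.** The test that is sized and named is not matched to the objective. An omnibus F-test, or its rank version, addresses whether the three time means differ at all. A reader of the results will want to know how much each marker changed by day 1 and by day 3–4, and how precisely. The plan commits to neither estimate.

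The form of the test is also left open. Normality tests are announced first, and the parametric or nonparametric version then follows as seems fit. Different markers could be analysed by different methods chosen after seeing the data, and those sent to a rank test would lose power and have no effect estimate on a usable scale.

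Finally, classical repeated-measures ANOVA and Friedman's test both need all three values. A patient with valid baseline and day-1 samples but no third sample contributes nothing, even to the early effect.

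**Working it through.** **Inputs.** From section 3.1: f = 0.25, alpha = 0.05, power 95%, m = 3 measurements, N = 58 raised to 65. The article gives no within-patient correlation (ρ), sphericity correction (ε), missing-data pattern or marker distribution. Those below are assumptions.

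**1. The plan's own figure.** For one group and ε = 1, λ = f²·N·m/(1 − ρ), with df = 2 and 2(N − 1).
- The smallest N for 95% power is 43 at ρ = 0.5, 51 at 0.4, 60 at 0.3 and 84 at 0.
- N = 58 is reached at about ρ = 0.32: λ = 0.0625 × 58 × 3 / 0.68 = 15.99, df 2 and 114, power 95.2%.
- So 58 does not follow from the stated inputs alone, but it is not shown to be wrong. I use ρ = 0.32 (the value that reproduces 58) and ρ = 0.5.
- Dropout: 58 / (1 − 0.10) = 64.4, rounded up to 65. This reproduces. The loss allowed is 7/65 = 10.8%.

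**2. Cost of moving to a rank test.** With m = 3, the asymptotic efficiency of Friedman's test under normality is (3/π) × m/(m + 1) = 9/(4π) = 0.716. Then 58 × 0.716 = 41.5 effective patients.

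| ρ | ANOVA, N = 58 | Friedman, effective N = 41.5 |
|---|---|---|
| 0.32 | λ = 15.99, power 95.2% | λ = 11.44, power 85.3% |
| 0.5 | λ = 21.75, power 98.9% | λ = 15.56, power 94.4% |

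Simulation gave the same picture: log-normal data, log-SD 0.2 to 1.0, N = 58, 1,500 runs per setting, Friedman used if Shapiro–Wilk rejected at any time point. Choosing by normality test had power of 85–88% (ρ = 0.32) or 94–96% (ρ = 0.5). ANOVA on the log scale had 95–96% or 98–99%. Rejection under the null was 4–6% for both, so the cost is efficiency, not type I error.

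**3. What the omnibus power says about the two questions.** Take two contrasts per marker, each at 0.025, with a paired-t approximation and N = 65.
- Means (0, d, d): f = 0.25 gives d = 0.53 SD. Power for each contrast is 91% (ρ = 0.32) or 97% (ρ = 0.5).
- Means (0, d/2, d): f = 0.25 gives d = 0.61 SD, so the day-1 change is 0.31 SD. Power for the day-1 contrast is 43% or 57%; for the late contrast it is 97% or more.

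The same f of 0.25 can therefore leave the early effect well or poorly covered, which the omnibus calculation hides.

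**4. Dropping patients without a third sample.**
- Power of the omnibus test with 58 complete patients against all 65: 95.2% and 97.1% (ρ = 0.32), 98.9% and 99.5% (ρ = 0.5).
- Worst case for bias: the 7 lowest day-1 values lose the third sample. With p = 7/65, z = −1.239 and density 0.185, the day-1 mean of the remainder shifts by 0.185/0.892 = 0.208 SD. At ρ = 0.5 the baseline mean shifts by 0.104 SD. The early effect is inflated by 0.104 SD, from 0.53 to 0.63.
- Softer dependence on the day-1 value, same 10.8% loss, 2,000 runs: +0.048 SD at ρ = 0.5 (+0.066 at ρ = 0.3) for complete cases, and about 0 for a likelihood analysis of all data. For scale, the standard error of the early contrast at N = 58 and ρ = 0.5 is √(2 × 0.5/58) = 0.13 SD.
- Missingness driven by the unseen day 3–4 value: late effect +0.047 SD for complete cases and +0.064 SD for the likelihood analysis. The model does not help here.

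**The case against.** The article condenses a fuller document, and missing-data rules, post-hoc contrasts and transformations often sit in an analysis plan that is not shown. That is fair, and their absence alone is not the point. What the article does state is an omnibus test, sized as such, with its form left open, set against an objective that asks for two effects.

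The figures depend on assumptions. At ρ = 0.5 Friedman's test still has 94% power. The efficiency of 0.72 holds under normality, whereas a rank test would be used when normality is rejected. This is partly met: ranks do not change under a log transformation, so for a marker that is normal after logs the same loss applies against a log-scale analysis. Against ANOVA on strongly skewed raw values (log-SD 1.0), Friedman's test does better: 86% against 72% at ρ = 0.32.

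Four stronger readings are tempting and should not be drawn:
- That the plan is expressly a complete-case analysis, or names Friedman's test. It does neither; both are inferred from the classical methods. The link from the normality tests to the repeated-measures choice is likewise implied, not stated.
- That discharge causes missing third samples. Section 2.3 links discharge to the timing of that sample, not to its absence, and the dropouts in section 3.1 are not defined.
- That a mixed model removes the bias. It does so only if missingness depends on observed values.
- That paired data would be tested with an unpaired test, because section 3.2 says the Mann–Whitney "U test will be used for those without a normal distribution". That sentence concerns continuous variables in general. The sentence after it assigns comparisons between time points to repeated-measures ANOVA, and a single-arm cohort still has independent subgroups, such as patients with and without kidney injury.

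**Conclusion.** The point holds in a limited form. The named primary analysis does not estimate the early and late effects that the objective asks for, and leaving its form to normality tests can cost up to about 10 points of power (95% to 85% at ρ = 0.32) or about 5 points (99% to 94% at ρ = 0.5). Keeping patients who lack a third sample is a secondary gain at the planned loss: 2 points of power or less, and about 0.05 SD of bias avoided under plausible day-1-driven missingness, 0.10 SD in the worst case. All these sizes rest on assumed correlation, distribution and missingness. The validity of the test under the null is not in question. This should be changed, but it does not undermine the study.

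**What to change.** For each marker, prespecify one linear mixed model with time as a categorical factor, unstructured covariance, and all patients with at least one sample. State the scale in advance: log for markers expected to be skewed, such as D-dimers, with a reason given per marker. Report day 1 versus baseline and day 3–4 versus baseline with 95% confidence intervals (as geometric mean ratios where logs are used). Drop the normality tests as the means of choosing the method.

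Record and report the actual day of the late sample, with a sensitivity analysis by day. Say plainly that the day is itself linked to recovery, so this describes the timing problem and does not remove it. State that the model is unbiased for missing samples only if missingness depends on observed values.

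The cost is wording: SPSS, already planned, fits such models, and no further patients or samples are needed beyond recording the sampling day. The downside is an assumption about scale for each marker, which the article at present gives no data to support.

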### 2.7. Outcomes

The primary outcome is to evaluate the effects of complex EVAR of para-renal and TAAA on coagulation with respect to von Willebrand factor (vWF), factors VIII and XI, D-dimers, fibrinogen, and Adamts-13 levels and on platelet activation (multiplate).

Perioperative laboratory tests will be performed according to institutional guidelines. These include a complete blood count, conventional coagulation tests, and kidney and liver function tests. In addition, the following parameters will be determined: vWF, factors VIII and XI, D-dimers, fibrinogen, Adamts-13, platelet activation (multiplate), and high-sensitivity troponin (hs-cTNT). The blood samples will be taken at three points in time: preoperatively before induction to general anesthesia, early postoperatively (1st postoperative day), and late postoperatively (3rd–4th postoperative day). The anti-Xa value, correlated to the weight and the dose of the anticoagulant, will also be determined in order to rule out an anticoagulant effect on the laboratory tests.

MINS, MACE, AKI, PIS, implant failure, and death from any cause during hospitalization were defined as secondary outcomes. MACE, implant failure (including secondary sac rupture, graft explantation, type 1 or 3 endoleak or major mitigation of the stent grafts), and death from any cause at 1, 3, 6, and 12 months postoperatively were also defined as secondary endpoints [21].

MINS is defined as postoperative hs-cTNT concentration 20 to 65 ng/L with an absolute change of >/=5 ng/L or any postoperative absolute value >/=65 ng/L [22,23].

MACE is defined as myocardial infarction (any clinical symptom associated with an acute coronary syndrome and/or any new electrocardiographic sign or high-sensitivity troponin elevation), arrhythmia (any event of atrial or ventricular tachycardia with more than 90 pulses per minute or any episode of bradycardia of less than 50 pulses per minute), and stroke (any transient ischaemic attack, any stroke: major or minor according to Rankin Score) [24].

PIS is defined as the presence of at least two of the systemic inflammatory response syndrome (SIRS) criteria, including fever >38 °C and leucocytosis >12,000/μL and obvious clinical or biochemical sign of infection (negative urine and blood cultures and chest X-ray) [24].

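### Univariate p<0.1 screening with backward elimination in 58 to 65 patients cannot support independent risk factor claims for seven continuous markers, and odds ratios are offered with no dichotomy defined

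*Protocol article*

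**What the plan says.** The protocol article, section 2.7, defines the primary outcome as the effect of complex EVAR on von Willebrand factor, "factors VIII and XI, D-dimers, fibrinogen, and Adamts-13 levels and on platelet activation (multiplate"), sampled before surgery, on day 1 and on day 3 or 4. These are seven continuous measures, and no cut-off is given for any of them.

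Section 3.2 plans univariate and multivariable linear or logistic regression, as appropriate, "with backward stepwise elimination for the assessment of independent risk factors contributing to our primary outcome". The next sentence says the final multivariable model will contain variables with p "values < 0.1 in the univariate regression, while the choice of variables will also be based on scientific knowledge". Results are to be given as odds ratios or regression coefficients, as appropriate, with p<0.05 significant throughout. A separate sentence adds: "Sensitivity and specificity analyses will also be performed using the Receiver Operating Characteristic Curves (ROC"). It names neither a marker nor an outcome.

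Section 3.1 sizes the study on the within-patient comparison alone: "considering an effect size = 0.25, a = 0.05, and 95% power, 58 patients should be included in the study", raised to 65 for dropout.

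**The concern.** Three points follow from the text.

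1. Variables are to be chosen by their p-values in the same 58 to 65 patients, and the survivors are then to be reported with ordinary p-values and confidence intervals. Those intervals assume that the model was fixed beforehand. Nothing labels the result exploratory.
2. The selection rules do not agree. Backward elimination drops variables. A final model that contains those passing p<0.1 does not. Two analysts could reach different models from the same data while both followed the text.
3. An odds ratio for the primary outcome needs an event, and none is defined for any of the seven markers.

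At stake is what the paper will say about who develops a stronger coagulation response. Section 5 expects the results to guide the design of later studies, so false or exaggerated factors would carry forward. The main comparison over time is not affected.

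**Working it through.** **The plan's own figure.** Section 3.1 gives f = 0.25, alpha 0.05, power 95% and three measurements in one group. With noncentrality f² × N × 3 / (1 − rho) and sphericity, N is 43 at rho = 0.5, 60 at rho = 0.3 and 58 at rho = 0.32. The correlation is not stated, so 58 can be reached and is not shown to be wrong. Also 58 / (1 − 0.10) = 64.4, which rounds up to 65. Neither figure was derived for the regression.

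**Inputs for the regression check**
- From the article: N = 58 and 65, seven markers, screen at p<0.1, significance at p<0.05.
- Assumed: 10 to 20 candidates. Table 3 and section 2.8 list about 15 patient and procedure items plus four events, but as data to collect, not as a covariate list.
- Assumed: removal at p≥0.10, normally distributed variables, and no true association unless stated.

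**Step 1, counting alone.** With k independent null candidates, the chance of at least one p<0.05 is 1 − 0.95^k: 40% (k = 10), 54% (15), 62% (19) and 64% (20).

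**Step 2, the stated procedure, one marker.** Simulated null data, N = 58, 3,000 datasets per setting, share with at least one retained factor at p<0.05:

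| Candidates | Screen, then backward elimination | Screen only, all p<0.1 kept |
|---|---|---|
| 10 | 42% | 39% |
| 15 | 53% | 49% |
| 20 | 66% | 58% |

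Repeat runs of the full procedure gave up to 43% (10 candidates), 54% (15) and 67% (20). With candidates correlated at 0.3 the rates fall to 36% (10), 48% (15) and 53% (19). N = 65 gives essentially the same rates. The closeness to step 1 shows that these figures mostly reflect how many candidates are tested.

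**Step 3, seven markers.** N = 58, markers and candidates each correlated at 0.3, 500 datasets per setting: at least one false factor in 92% (10 candidates), 98% (15) and 99% (19). The average number of false factors is 2.6, 4.0 and 4.6.

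**Step 4, the effect of selection itself.** With 15 candidates, one of which has a true standardised slope of 0.25, the mean estimate when that variable is retained is 0.33 at N = 58 (0.33 / 0.25 = 1.32, so 32% too large) and 0.31 at N = 65. For noise factors retained after elimination, the nominal 95% interval contains the true value of zero in only 40%, 39% and 34% of cases with 10, 15 and 20 candidates.

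**Step 5, if a marker were dichotomised.** An assumed event share of 10 to 30% gives 58 × 0.10 = 5.8 to 58 × 0.30 = 17.4 events. That is about 0.3 events per candidate at the low end (5.8 / 19) and 1.7 at the high end (17.4 / 10).

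**The case against.** The strongest replies are these.

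- **The text allows linear models.** This stands. Linear regression with coefficients fits the markers, and the criticism of odds ratios concerns only the other option. It does not rescue the selection procedure, since steps 2 to 4 use linear models throughout.
- **The false-factor rates are a counting effect.** This largely stands. A fixed list of five terms for each of seven markers is 35 tests, and 1 − 0.95^35 = 83% under the null. A fixed list therefore does not make false positives rare. Its gains are honest estimates and intervals, fewer tests, and an exploratory label in place of a claim.
- **Variable choice also rests on scientific knowledge.** True, and it may shorten the list. It is not a list fixed in advance, so it leaves discretion.
- **The article names no covariates because an analysis plan may do so.** Accepted. The absence of a covariate list, including the marker's baseline value, is not held against it. The screening and elimination rules are stated, so they can be judged.
- **The regression is ancillary.** True. The repeated-measures comparison stands apart from it.

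A reader might also infer that the ROC curves are meant for the non-binary primary outcome, or that cut-offs will be chosen after seeing the data. The article supports neither. The ROC sentence names no outcome, and binary secondary outcomes such as MINS and AKI exist. Cut-offs could be fixed in a document not shown.

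**Conclusion.** The point holds for the risk-factor analysis only. The planned selection in 58 to 65 patients gives at least one false factor in about 40 to 67% of single-marker analyses with 10 to 20 independent candidates, somewhat less if candidates are correlated. Across all seven markers the figure is about 92 to 99%. Both ranges assume a complete null, an assumed candidate count and an assumed removal level, and mostly measure the number of candidates. The damage due to selection itself is the inflation of retained effects (0.25 reported as about 0.33 at 58 patients) and invalid intervals for retained noise factors.

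The conflict between the two selection rules and the offer of odds ratios without a dichotomy can be read directly from section 3.2. It would go too far to say that false factors are certain for any one marker: near certainty applies only when all seven are modelled and no candidate truly matters.

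**What to change.** - Drop the univariate screen and the stepwise elimination.
- For each marker, fit a linear model (log scale if skewed) at day 1 and at day 3 to 4, or one mixed model covering both samples, on the marker's own baseline plus a short covariate list fixed before the data are examined.
- Report every coefficient with its 95% confidence interval as exploratory, and make no independent risk factor claim on p<0.05 alone.
- Remove logistic regression and odds ratios for the primary markers unless a cut-off is fixed in advance.
- Name the binary outcome for the ROC analysis, for example MINS. Report the AUC with its confidence interval, and do not present a cut-off derived from these data as validated.

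The cost is a change of text, with no new data. The downside is that fewer candidate factors are examined.

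### Seven unranked laboratory markers share the primary outcome, each judged at p < 0.05 with no multiplicity control stated; the 5% error and 95% power hold only for one marker tested alone

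*Protocol article*

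**What the plan says.** All references are to the protocol article.

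- **Primary outcome.** Section 2.7 defines it as the effect of complex EVAR on coagulation, judged on "von Willebrand factor (vWF), factors VIII and XI, D-dimers, fibrinogen, and Adamts-13 levels and on platelet activation (multiplate". That is seven markers: vWF, factor VIII, factor XI, D-dimers, fibrinogen, Adamts-13 and platelet activation. None is named as the lead marker, and no rule says how many must change.
- **Timing.** Section 1.3 labels the same list the primary endpoint and includes two time frames: "To evaluate the early (postoperative day one) and late (postoperative day 3 or 4) effects of complex EVAR".
- **Hypothesis.** Section 1.2 says the study will assess whether complex EVAR produces a more severe coagulation response with more marked platelet activation.
- **Sample size.** Section 3.1 states "Our study will include one group arm" and uses a within-factors repeated-measures F-test with three measurements per patient. Its inputs and result are given as "considering an effect size = 0.25, a = 0.05, and 95% power, 58 patients should be included in the study". The number is raised to 65 for dropout. The marker to which the calculation applies is not named.
- **Analysis.** In section 3.2, repeated-measures ANOVA, parametric or nonparametric, "will be used for the evaluation of possible differences among parameters measured at different time points". The section ends with the p-value rule "values < 0.05 will be considered significant".

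**The concern.** Three things that the article fixes do not fit together: an outcome made of seven markers, a sample size for one test at the full alpha, and a threshold of 0.05 for every test. Followed as written, the plan runs seven primary tests at 0.05 each, and nothing in it limits the joint error for a general statement that complex EVAR affects coagulation.

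The study's main claim is at stake. Section 5 expects the results to guide the design of later studies. One unadjusted positive among seven would be weaker evidence than the nominal 5% suggests, and a lead marker or a correction chosen after the data have been seen would not be credible.

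**Working it through.** **Inputs from the article.** K = 7 primary markers (2.7); m = 3 measurements, one group, f = 0.25, alpha = 0.05, power 95%, N = 58, raised to 65 (3.1).

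**Not given, so assumed and varied.** The correlation rho between repeated measurements of a marker, the nonsphericity factor eps, and the correlation r between markers.

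**1. The plan's own figure.** Noncentral F with lambda = f² × N × m × eps / (1 − rho), df1 = (m − 1) × eps, df2 = (N − 1)(m − 1) × eps.

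- rho = 0.5, eps = 1: 95% power needs N = 43.
- rho = 0.32, eps = 1: lambda = 0.0625 × 58 × 3 / 0.68 = 15.99, df 2 and 114, power 95.2%. N = 58 is the smallest that reaches 95%.
- rho = 0.6, eps = 0.5: lambda = 0.0625 × 58 × 3 × 0.5 / 0.4 = 13.59, df 1 and 57, power 95.2%. N = 58 again.

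The 58 is therefore reachable for one test at alpha 0.05, but cannot be confirmed without rho and eps. The step to 65 agrees with a 10% dropout allowance: 58 / 0.90 = 64.4, rounded up to 65.

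**2. Family-wise error, seven tests at 0.05, all nulls true.**

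If independent: 1 − 0.95⁷ = 0.302.

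If correlated: simulated repeated-measures F-tests for seven equally correlated markers, n = 58, 20,000 runs per setting (Monte Carlo standard error about 0.3 percentage points at most).

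| r between markers | Any of 7 at 0.05 | Any of 7 at 0.05/7 |
|---|---|---|
| 0 | 30% | about 5% |
| 0.3 | 27% | under 5% |
| 0.5 | 24% | about 4% |
| 0.7 | 19% | under 4% |
| 0.9 | 12% | about 2% |

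If some markers truly change, fewer nulls remain. With four independent true nulls the figure is 1 − 0.95⁴ = 18.5%.

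**3. Per-marker power at the adjusted level.** 0.05/7 = 0.00714. This is the strictest step of Holm's procedure, so it is a floor for Holm.

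| rho, eps | N = 58 | N = 65 | N for 95% |
|---|---|---|---|
| 0.6, 0.5 | 81% | 86% | 84 |
| 0.32, 1 | 82% | 87% | 82 |
| 0.5, 1 | 94% | 97% | 61 |

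The first two rows are pairs that give the stated 58 at alpha 0.05. The third is a more favourable assumption. Less favourable pairs go lower (rho = 0.5, eps = 0.5 gives 69% at 58), but that pair gives only 90% power at unadjusted 0.05, so it does not match the stated 95%.

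**4. If all seven markers had to change.** With 95% power for each and independence, joint power is 0.95⁷ = 0.698, about 70%.

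**The case against.** The strongest reply is that this is a single-arm observational study whose article describes effects marker by marker and promises better understanding, with no decision tied to a p-value. Read that way, each marker's statement keeps its own 5% error, and the any-of-seven rule is the reader's construction. The article is also condensed: an analysis plan that is not shown may contain an adjustment, and a 0.05 threshold is compatible with adjusted p-values.

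Part of this stands:

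- **A flat 30%.** A reader might infer it, but it needs independence and seven true nulls. Section 2.8 has the markers measured at the same sampling times in the same patients, so independence is unlikely. Only a range with its assumptions is supportable.
- **About 51% from 14 tests.** A reader might count early and late contrasts for seven markers: 1 − 0.95¹⁴ = 0.512. Section 3.2 prescribes no such set of unadjusted contrasts, and both contrasts share a baseline. Simulation of 14 such tests (n = 58, 4,000 runs) gave 49% with uncorrelated markers, 38–39% at r = 0.5 and 30% at r = 0.7. With contrasts run only after a significant overall test it was about 20% at r = 0.5.
- **One positive marker will be presented as a positive study.** The article does not say so. The error figures are conditional on that reading.
- **The 5% and 95% are meaningless, or 58 is wrong.** Neither follows. Both rates apply to one marker tested alone, and 58 is reachable.

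The rest does not remove the point. Section 1.2 states a hypothesis about the coagulation response as a whole, section 3.2 speaks of the primary outcome in the singular, and nothing calls the markers exploratory. An adjustment in an unseen plan would still need to be reconciled with the unsplit alpha behind the published sample size.

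**Conclusion.** The point holds in a conditional form. The article sets seven co-listed primary markers against one sample-size test at alpha 0.05 and one blanket threshold, with no multiplicity control stated. If a change in any marker counts as support for the coagulation hypothesis, the family-wise error is up to about 30% (independent tests, all nulls true) and about 12–27% for inter-marker correlations of 0.9 to 0.3. Even the lowest of these is more than twice the nominal level. The stated 5% and 95% are correct only as per-marker figures.

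The error range rests on equal inter-marker correlations and all nulls true. The adjusted-power range rests on assumed rho and eps. The documents supply none of these values.

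**What to change.** **Section 3.2.** Add a paragraph to this effect: the seven marker-level repeated-measures tests are adjusted by Holm's procedure at a family-wise 0.05; a marker is declared changed only if its adjusted p is below 0.05; early and late contrasts are tested within a marker only after its adjusted overall test is significant; all other p-values are descriptive. The 5% family-wise guarantee then covers the seven marker-level claims.

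**Section 3.1.** State that the 95% power is per marker at unadjusted alpha 0.05, report the rho and eps used, and give the per-marker power at 0.05/7 beside it. Under the assumed values above this is about 81–94% at 58 and 86–97% at 65 evaluable patients.

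Naming one lead marker, using a global test, or declaring the marker-level results exploratory would also settle the matter. Holm keeps all seven markers in the primary outcome.

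**Cost.** A short addition to each of two sections, made before the data are examined. No extra patients are needed if somewhat lower per-marker power is accepted. Keeping 95% per marker at 0.05/7 would take 61 to 84 evaluable patients under the same assumptions.
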